## Description of research methodology

This is a prospective, interventional, randomized, parallel-group clinical trial with a waiting-list design, in which subjects will be randomized using randomly sized block randomization.

[figure not shown]

**Figure 1** : Study design

## 6.3 Measures to minimize and avoid bias

Randomization will be performed using randomly sized blocks.
The primary objective of this study is to evaluate the effect of exposure to a musical intervention session during botulinum toxin injections on the stress induced by the injection. More specifically, this objective will be assessed at the first injection visit (Injection Visit 1).

As this is a waiting-list randomized study, patients who do not receive the musical intervention at Injection Visit 1 will be offered the intervention during the subsequent injection visit (Injection Visit 2). This design aims to improve acceptability of participation (acceptance of randomization compared to a standard parallel-group randomized trial), thereby enhancing study feasibility.

The comparison at Injection Visit 2 is a secondary objective, intended in particular to measure the effect of repeated exposure to the musical intervention and intra-individual variability before and after the intervention (assessed via mixed models for secondary endpoints; see section 10.4).

A crossover experimental design was considered but ultimately rejected, given that heart rate variability results could be influenced in patients receiving usual care at Injection Visit 2 after having undergone the musical intervention at Injection Visit 1. Furthermore, although it is unlikely that patients’ clinical status would change significantly between two injections, this possibility cannot be entirely excluded, representing a potential major bias (risk of carryover effect) for a crossover study. Finally, loss to follow-up or study discontinuation would have a greater impact on a crossover design compared to the proposed waiting-list design, where the primary objective is assessed at Injection Visit 1.

A strictly anonymous list of patients who decline to participate in the study will be maintained to report inclusions in the flowchart and to analyze the representativeness of the patient sample included in the study.

# PRACTICAL IMPLEMENTATION OF THE PROTOCOL

## Detailed description of procedures performed on participants (description of each visit)

**V0 (Month -4 to Month -1): Pre-screening visit**
Patients will be selected during routine consultations in the Physical Medicine and Rehabilitation (PMR) department. They will receive the study information sheet and will have a minimum of one month and a maximum of three months to provide informed consent and be included at the next consultation.

**V1 (Month 0): Injection visit 1 (inclusion visit)**
At this visit, informed consent will be obtained from the patient or their legal guardian. The physician will provide a copy of the signed consent form to the patient or their legal representative/trustee/designated person. The following data will be collected: age, sex, pathology, and date of first botulinum toxin injection. Once this information is recorded, randomization will be performed by the Clinical Research Associate (CRA) of the department.
For all injections, the same standardized protocol will be applied for each patient (ultrasound-guided or electromyography localization technique, MYOBOT needle [26G], analgesia by ice for palmar or plantar injections upon patient request) in an outpatient setting.

During the first injection visit, a Polar H10 heart rate monitor chest strap will be placed on the patient to measure stress induced by the medical procedure. A minimum recording period of 10 minutes is required prior to the injections to collect reliable baseline data. During this time, the physician will prepare the syringes for botulinum toxin injection. The patient will complete the self-administered anxiety questionnaire (STAI-Y1).

The control group (CT-IM) will not receive any specific intervention other than the Polar H10 heart rate monitor. This group will undergo botulinum toxin injections according to usual practice within the department, with the same evaluations as the intervention group (IM-IM).

The intervention group (IM-IM) will receive a tablet and headphones to listen to music during the botulinum toxin injections. Before the injection, during the waiting time, the patient, with or without assistance, will choose the music to listen to based on personal preferences. The music duration can be adjusted to fit the length of the medical procedure.

At the end of the injection session (both groups), a Visual Analog Scale (VAS) will be presented to the patient to rate pain on a scale from 0 to 10. The nurse or CRA will ask the patient to rate their satisfaction with the intervention using a VAS. Anxiety will be measured using the STAI-Y1 questionnaire. Time perception will also be evaluated based on patient self-report and compared to the actual duration of the medical procedure.

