# STUDY METHODOLOGY

## Evaluation criteria

### Primary endpoint

Patient stress, assessed during Injection Visit #1, will be estimated by changes in Heart Rate Variability (HRV), measured before and during the botulinum toxin injection session using the LF/HF ratio.

The LF/HF ratio is a reliable indicator of the balance between sympathetic and parasympathetic nervous system activity. It provides insight into stress regulation, cardiovascular health, and physiological adaptation. A lower LF/HF ratio may be associated with improved recovery, better emotional regulation, and a healthier autonomic nervous system balance.

HRV will be measured using a Polar H10 heart rate monitor belt. Data will be exported to the Elite HRV application and analyzed using KUBIOS software.

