### Secondary endpoints

- Patient stress during Injection Visit #2, estimated by changes in HRV, measured before and during the botulinum toxin injection session using the LF/HF ratio.
- Pain intensity experienced by the patient during Injection Visits #1 and #2, measured immediately after the injection session using a simple Numerical Rating Scale (NRS) ranging from 0 (“no pain”) to 10 (“worst imaginable pain”).
- Anxiety variation measured by the self-administered State-Trait Anxiety Inventory - Form Y, State subscale (STAI-Y1) during Injection Visits #1 and #2, before and after the botulinum toxin injections. The STAI-Y1 consists of 20 items rated on a 4-point Likert scale, from 1 (“Not at all”) to 4 (“Very much”) (see ANNEX 2).
- Patient’s perception of the duration of the session relative to the actual injection time during Injection Visits #1 and #2. This self-reported data will be collected at the end of each session.
- Patient satisfaction with the intervention assessed using a Visual Analog Scale (VAS) ranging from 0 (“no satisfaction”) to 10 (“highest satisfaction”), measured after the injections during Visits #1 and #2.
- Quality of the botulinum toxin injection conditions, as assessed by the physician immediately after each session during Visits #1 and #2, using a simple Numerical Rating Scale (NRS) from 0 (“extremely poor conditions”) to 10 (“extremely good conditions”).

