## Dosage, administration modalities and duration

The headphones will be worn before and throughout the entire duration of the medical procedure. The patient must remain on the examination table for the entire duration of the measurements.

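### Visit 1 is narrated with randomisation before the baseline HRV recording and the first STAI-Y1, and nothing withholds allocation until both are complete

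*Protocol*

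**What the plan says.** Section 7.1 (V1) lists what is recorded after consent: "The following data will be collected: age, sex, pathology, and date of first botulinum toxin injection". It continues: "Once this information is recorded, randomization will be performed by the Clinical Research Associate (CRA) of the department". Neither HRV nor STAI-Y1 is on that list.

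The next paragraph but one describes the chest strap and the baseline: "A minimum recording period of 10 minutes is required prior to the injections to collect reliable baseline data". The first STAI-Y1 is completed in the same period. For the music arm (IM-IM) the section adds: "Before the injection, during the waiting time, the patient, with or without assistance, will choose the music to listen to based on personal preferences". The control arm (CT-IM) receives nothing beyond the heart rate monitor; no sham or control audio is planned. Section 8.2 adds: "The headphones will be worn before and throughout the entire duration of the medical procedure".

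Both endpoints are changes from these values. The primary endpoint (6.1.1) is the change in HRV "measured before and during the botulinum toxin injection session using the LF/HF ratio". The anxiety endpoint (6.1.2) is the variation in STAI-Y1 "during Injection Visits #1 and #2, before and after the botulinum toxin injections". Section 10.3 compares the LF/HF change between arms by a t-test or Mann-Whitney test. Section 6.3, on measures against bias, does not say when allocation is made known to the patient.

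**The concern.** A change score protects against chance baseline differences only if the baseline is untouched by allocation. Here the outcomes are stress and state anxiety, which news of the assigned arm could plausibly move. A music-arm patient may feel relief, and a control patient may feel disappointment. If that reaction shifts the 'before' value, the shift passes one for one, with opposite sign, into the between-arm difference in change.

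STAI-Y1 is a questionnaire filled in by the patient, so knowledge of the arm can act on it directly. LF/HF is recorded by a device, so only a real physiological reaction to allocation could move it. At stake are the primary comparison and the anxiety comparison at visit 1. No later analysis can recover a pre-allocation baseline that was never measured.

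**Working it through.** **Step 1: order of events in section 7.1 (V1).**

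1. Consent, then age, sex, pathology and date of first injection.
2. Randomisation, expressly triggered by completion of item 1.
3. Strap, baseline recording of at least 10 minutes, first STAI-Y1 (described next, without an explicit 'after randomisation').
4. Music choice in IM-IM, before the injection.
5. Injections, then the end-of-session measures.

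What precedes randomisation is explicit. That item 3 follows it comes from the narrative order.

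**Step 2: can patients know their arm at item 3?** The text does not say when they are told. An IM-IM patient must know by the time music is chosen and headphones are fitted, both before the injection. A CT-IM patient could infer the arm from the absence of a tablet. No section delays disclosure.

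**Step 3: the plan's own figure (10.1).** Inputs: difference 1.8, SD 2.3, two-sided 5%, power 90%, 1:1 allocation.

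n = 2 (1.960 + 1.282)² (2.3 / 1.8)² = 2 × 10.51 × 1.633 = 34.3, so 35 per group.

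This reproduces the stated 35. The t-based solution is 35.3, with power 89.7% at 35 and 93.3% at 40 per group. No sample-size error is raised.

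**Step 4: illustration.** Let b be the amount by which learning the allocation lowers the 'before' LF/HF in IM-IM relative to CT-IM. The documents give no value for b; 0.25 and 0.5 are assumptions. Hold the during-session difference at 1.8 in favour of music. The expected difference in change is then

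Δ = 1.8 − b,

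and power comes from the noncentral t with 2n − 2 degrees of freedom and noncentrality Δ / (2.3 √(2/n)). The standard error is 2.3 √(2/35) = 0.550 at 35 per group and 2.3 √(2/40) = 0.514 at 40.

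| b | Δ | Power, 35 per group | Power, 40 per group |
|---|---|---|---|
| −0.5 | 2.30 | 98.5% | 99.3% |
| −0.25 | 2.05 | 95.7% | 97.6% |
| 0 | 1.80 | 89.7% | 93.3% |
| 0.25 | 1.55 | 79.4% | 84.5% |
| 0.5 | 1.30 | 64.5% | 70.4% |

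Negative b (a lower control baseline) inflates the apparent effect of music.

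**Step 5: no during-session difference.** Then the absolute value of Δ is that of b, and the two-sided test at 5% rejects as follows for either sign:

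| Size of shift | 35 per group | 40 per group |
|---|---|---|
| 0.25 | 7.3% | 7.7% |
| 0.5 | 14.6% | 16.0% |

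No figure is offered for STAI-Y1, because the protocol gives neither an expected difference nor an SD for it.

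**The case against.** The strongest reply is that the protocol never says patients know their arm at baseline. The paragraph on the strap and STAI-Y1 carries no explicit 'after randomisation'. Figure 1 and Annex 1, which might show the sequence, are not reproduced in the text available here. This stands as a limit on certainty. It does not remove the point: the narrative places randomisation first, and nothing in 7.1 or 6.3 says otherwise.

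Several stronger readings are tempting but not supported:

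- **That both 'before' values certainly come from patients aware of their arm.** This is a reasonable inference, not a statement in the text, and it is weaker for controls.
- **That music is chosen, or already playing, during the 10-minute baseline at visit 1.** Section 7.1 speaks of the waiting time without equating it with the recording. Section 8.2 has headphones worn beforehand without saying how long or whether music is on.
- **That a baseline-adjusted analysis would be contaminated as well.** Sections 10.2 to 10.4 provide for adjustment for imbalanced factors and covariates such as sex and age; pre-injection LF/HF is not named.
- **That power will fall by the amounts shown.** The shifts are assumed and could favour either arm. The 1.8 is itself a difference in change, based on an earlier study by the team. Whether it was free of a similar effect cannot be checked.

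Section 6.3 also offers little evidence of an emotional reaction: it presents the waiting-list offer as an aid to acceptability and feasibility. Finally, STAI-Y1, where the argument is most direct, is an exploratory secondary endpoint (10.2).

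**Conclusion.** The point holds as a weakness in the order of procedures that the protocol should correct. As narrated, randomisation comes before both baseline measures in an open trial with change-score endpoints, and concealment until the baselines are complete is not stated. The 'before' values may therefore be influenced by allocation.

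Confidence is high on when randomisation is triggered and moderate on whether patients know their arm at baseline. The risk is clearest for STAI-Y1. For LF/HF the existence, size and sign of any bias are unknown. Under assumed shifts of 0.25 to 0.5 LF/HF points, SD 2.3 and a during-session difference held at 1.8, power at 35 per group would lie between 65% and 79% if the shift went against music. The false-positive rate would be about 7% to 15% for a shift of either sign. These figures show sensitivity and are not estimates. The planned 35 (40) per group is unaffected.

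**What to change.** Reorder section 7.1 (V1) as follows:

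1. Consent and descriptive data.
2. Strap placement, first STAI-Y1 and the baseline recording of at least 10 minutes.
3. Randomisation, or at least disclosure of the result.
4. Music choice and headphone fitting in IM-IM, with a matched short interval in CT-IM.
5. Injections.

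Add a sentence to section 6.3 that allocation is revealed only after both baseline measures are complete. If the sponsor already intends this, the sentence and an explicit sequence in 7.1 are enough.

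The cost is a few more minutes in the visit and a slightly longer gap between baseline and injection, with the patient staying on the examination table. The same CRA randomises at the same visit, with no extra equipment and no change in sample size.

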**V2 (Month 3 ± 1 month): Injection visit 2**
At this visit, both groups will receive a tablet and headphones to listen to music during the botulinum toxin injections. The musical intervention, as described below, will begin immediately after the medical consultation and completion of the STAI-Y1 anxiety questionnaire. The CRA or nurse will set up the patient on the medical bed and place the Polar H10 chest strap. The patient, with or without assistance, will choose the preferred music. During a resting period of at least 10 minutes, the patient will listen to the selected music. The music duration can be adjusted to match the length of the medical procedure.

At the end of the injections (both groups), a Visual Analog Scale (0 to 10) will be used to assess perceived pain. The nurse or CRA will ask the patient to rate their satisfaction with the intervention via VAS. Anxiety will be quantified using the STAI-Y1 questionnaire. Time perception will again be assessed via self-report.

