## General logistical organization of the trial

The trial will be conducted within the PMR department of the Clermont-Ferrand University Hospital. The implementation of the musical intervention and its explanation will be coordinated by a nursing assistant (NA).

Patients will be provided with dedicated headphones and will be trained by the NA, who assists the physician during the procedure, to operate the tablet interface. The nursing assistant has been trained and is qualified to select an appropriate musical program based on the patient’s preferences (MUSIC CARE® Paris, France), if necessary.

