## Product presentation

A pair of headphones and a tablet will be available for the entire duration of the study. The headphones will be placed on the patient’s ears once they are positioned on the examination table. The nurse assisting the physician during the botulinum toxin injections will help the patient select the music they wish to listen to. Additionally, the patient may navigate through the application to modify the music style or adjust the duration of the listening session, if desired. The objective is to ensure that the listening duration extends throughout the medical procedure, continuing until the completion of the injections. The listening session may also be controlled by the investigator or the nurse, who can stop the device at any time.

[figure not shown]

**Figure 3** : Application MUSIC CARE^®^

The MUSIC CARE® application is available for download on various platforms (AppleStore or PlayStore). The PMR department will have an account to allow patients to benefit from this therapeutic approach. The first image in Figure 2 shows the different session choices based on the patient’s preferences. In the context of the MUSIBOT study, the application will be used with the aim of reducing stress related to the medical procedure. A diagram is then presented to explain to the patient the "U-shaped" sequence. Once the patient selects the "pain" program, another page appears, allowing the patient to choose the music style they wish to listen to during the session. Music can be selected by category. The patient selects the music to listen to and is then asked to rate their current level of pain using a Visual Analog Scale (VAS). The music begins according to the "U-shaped" sequence, with a minimum duration of 20 minutes. The duration can be adjusted based on the length of the medical procedure. The patient/nurse controls the application and can modify settings as needed.

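### At visit 1, satisfaction is requested by staff who know the arm and may have helped with the music, so courtesy may inflate it more in the music arm than in controls

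*Protocol*

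**What the plan says.** Section 7.1 of the protocol describes how satisfaction is collected. At visit 1, in both groups: "The nurse or CRA will ask the patient to rate their satisfaction with the intervention using a VAS". At visit 2 the wording is nearly the same: "The nurse or CRA will ask the patient to rate their satisfaction with the intervention via VAS".

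On the people involved, 7.1 says that "randomization will be performed by the Clinical Research Associate (CRA) of the department". Section 8.3 (Product presentation) says: "The nurse assisting the physician during the botulinum toxin injections will help the patient select the music they wish to listen to". It adds that the patient or nurse controls the application. The visit 1 text in 7.1 is looser: "the patient, with or without assistance, will choose the music to listen to based on personal preferences". Section 7.2 names another role: "The implementation of the musical intervention and its explanation will be coordinated by a nursing assistant (NA"), and lets that person pick a programme if needed.

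On the comparator at visit 1: "The control group (CT-IM) will not receive any specific intervention other than the Polar H10 heart rate monitor". That group is nevertheless followed "with the same evaluations as the intervention group (IM-IM").

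Satisfaction is a secondary endpoint on a 0 to 10 visual analogue scale (6.1.2). The arms are compared by t-test or Mann-Whitney test (10.4), and 10.2 declares the secondary analyses exploratory.

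**The concern.** Satisfaction is a courtesy-prone outcome: a patient asked by a member of staff tends to answer kindly about what that person has just done. At visit 1 only the music arm has received something extra, and the person asking may be the one who helped to choose it and ran the tablet. The control patient is asked by staff who delivered nothing beyond usual care and the chest strap. The pressure to please can therefore differ between arms, most plausibly in favour of music.

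Patients cannot be masked to music, so some reporting bias has to be accepted. The part that comes from who requests the rating does not. Visit 1 is the only visit with a control group without music, so it is where a satisfaction difference would be read as an effect of the intervention. Neither randomisation nor more patients removes a bias of this kind.

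**Working it through.** **The plan's own figure.** Section 10.1 gives 35 per group for the LF/HF ratio: n = 2 × (1.960 + 1.282)² × (2.3/1.8)² = 2 × 10.51 × 1.633 = 34.3, rounded up to 35. It reproduces, but it concerns the primary endpoint and has no bearing here. The protocol states no standard deviation, difference or power for satisfaction, so the point rests mainly on setting the text side by side.

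**Step 1: do the askers know the arm?** Yes. The CRA performs the randomisation (7.1). A nurse present at the injections sees whether the patient is wearing headphones.

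**Step 2: can the asker have helped with the music?**
- 8.3: the nurse assisting the physician helps to select it.
- 7.1, visit 1: assistance is optional and the helper is not named.
- 7.2: a nursing assistant, also described as assisting the physician, coordinates the intervention, trains the patient and selects a programme if necessary.
- 7.1: the asker is the nurse or the CRA.

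On the 8.3 wording the nurse can be both helper and asker. If the CRA asks, or the nursing assistant is a different person from the nurse, the roles are separate. The protocol permits the overlap and does not settle it.

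**Step 3: does the situation differ between arms?** At visit 1, yes: the music arm has had the music and possibly help with it, while controls have had neither. At visit 2 both arms have music, so this contrast is absent.

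**Step 4: is there a safeguard?** Section 6.3, on measures against bias, covers randomisation, the waiting-list choice and a list of refusals. It does not address how patient-reported items are collected. The STAI-Y1 is described as self-administered, so a self-completion route already exists in the same session.

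**Step 5: do both arms answer the same question?** The item refers to the intervention. Visit 1 controls have none apart from the monitor, so what they are rating is unclear.

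**Step 6: size, purely as illustration.** Assume 40 per arm (10.1), no true difference, a two-sided 5% test, and a net reporting shift b in the music arm. Both b and the SD are assumptions; neither is in the protocol. With SE = SD × √(2/40) and SD = 2, SE = 0.447.
- b = 0.5: b/SE = 1.118, and P(|Z + 1.118| > 1.96) ≈ 0.20.
- b = 1.0: b/SE = 2.236, and P(|Z + 2.236| > 1.96) ≈ 0.61.

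The exact noncentral t calculation (78 degrees of freedom) gives:

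| Assumed SD | b = 0.5 | b = 1.0 |
|---|---|---|
| 1.5 | 31% | 84% |
| 2.0 | 20% | 60% |
| 2.5 | 14% | 42% |

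The nominal rate is 5%. The table shows that a small shift would matter if it existed. It does not show that one exists, nor how much of it would come from the staff request rather than from patients knowing their arm.

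**The case against.** The strongest case against is that this is a preference about how a form is handed over. The protocol contains no misstatement here, the endpoint is exploratory, and the primary endpoint is recorded by an instrument. Much of that stands, and it limits the weight of the point. Several stronger readings are tempting and are not supported:

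- *That courtesy acts in the music arm alone.* Controls have the same evaluations and can be polite about their care. The text supports a larger shift in the music arm, not one confined to it.
- *That the nurse who set up the music is the one who asks.* Assistance is optional in 7.1, 7.2 names a nursing assistant, and the CRA may do the asking. The overlap is allowed, not prescribed.
- *That the rating is spoken aloud and written down by staff.* Asking a patient to use a visual analogue scale is compatible with the patient marking it. The protocol does not say who makes the mark or who sees it.
- *That the false-positive rate is 20% to 61%.* Those values follow only from an assumed shift and an assumed SD. They also charge the whole shift to the staff request, although unmasked patients would show some of it on a closed form too.
- *That pain and perceived time are collected badly in the same way.* In 7.1 the pain scale is presented to the patient and time is self-reported, so nothing shown here calls for changing them.

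What survives is that an avoidable difference between arms is left open when the means to close it are already in the session.

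**Conclusion.** The point holds as a minor improvement. At visit 1 the rating is requested by staff who know the arm, and the protocol does not prevent the asker from being someone who helped with the music. Satisfaction may therefore be inflated more in the music arm than in controls, beyond what unmasked patients make unavoidable. The direction is plausible rather than demonstrated, and the size is unknown.

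The conclusion assumes that ratings respond to who asks, and that the overlap of roles occurs in at least some sessions. It affects an exploratory secondary comparison at visit 1. A reader might infer that it weakens the trial's main result; it does not, because the LF/HF ratio comes from the chest-strap recording. The unclear meaning of the item for visit 1 controls is the firmer part of the point, since it applies whoever asks.

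**What to change.** In 7.1, for both visits and identically in both arms:

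1. The patient marks the satisfaction scale alone, together with the self-administered post-session STAI-Y1, and hands it in closed.
2. The item asks about satisfaction with the injection session, so that visit 1 controls can answer it; 6.1.2 is worded to match.
3. Where a patient cannot write, an available staff member who did not help with the music records the answer where possible, and the assistance is noted on the form.
4. 7.1, 7.2 and 8.3 are reconciled on who helps with the music.

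Visit 2 is included so that its ratings are collected in the same way as those of visit 1, not because the same contrast between arms exists there.

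The cost is a few sentences and one added line on a form that is already handed out. The downside is that patients with upper-limb impairment will still need help, possibly more than a few in a population with spasticity, so the safeguard will be incomplete. Recording assistance lets its frequency be compared between arms.

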## Hypotheses and objectives

The hypothesis of this research is that a musical intervention can reduce stress in adults during botulinum toxin injections.

The primary objective of the study is to assess the effect of exposure to a musical intervention session during botulinum toxin injections on injection-induced stress, measured by Heart Rate Variability (HRV).

Secondary objectives include evaluating the effect of exposure to a musical intervention session during botulinum toxin injections on injection-induced pain and anxiety. Additionally, patient satisfaction regarding the injections following the musical intervention session will be assessed. The impact of the musical intervention on the medical procedure will be evaluated based on the physician’s appraisal at the end of the session. Finally, the patient’s perception of time during the session will also be evaluated.

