## Secondary analyses

The main analysis may be supplemented by a multivariate analysis using multiple linear regression to account for covariates selected based on univariate analysis results and their clinical relevance (including sex and age of the patients). Special attention will be given to the study of multicollinearity (Farrar and Glauber test and VIF indicator). The validity of the model (normality of residuals and homogeneity of variances) will be visually assessed. The results will be expressed in terms of regression coefficients, effect sizes, and 95% confidence intervals.

Subgroup analyses will be conducted for the primary endpoint, based on the sex and age of the patients. The interaction between group and subgroup will be explored. The results will be expressed in terms of regression coefficients, effect sizes, and 95% confidence intervals.

Analyses aimed at studying the effect of exposure to a music intervention session during botulinum toxin injections at visit #1, in terms of stress induced by the injection for HRV parameters other than LF/HF, pain induced by the injection, anxiety during the injections, patient satisfaction, and the effect of music intervention on the medical procedure (botulinum toxin injections) as expressed by the physician at the end of the session, will follow the same statistical analysis plan as for the primary endpoint.

Analyses to study the effect of exposure to a music intervention session at visit #2 (to evaluate the effect of repeated exposure to a music intervention) on the variation of stress, pain, variation of anxiety, patient satisfaction, and the effect of music intervention on the medical procedure (botulinum toxin injections) as expressed by the physician at the end of the session, will rely on mixed models.

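### At visit 1 both arms rate satisfaction with an intervention that controls do not receive, so the between-arm satisfaction test does not clearly compare one construct

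*Protocol*

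**What the plan says.** Protocol section 6.1.2 (Secondary endpoints) defines the endpoint as "Patient satisfaction with the intervention assessed using a Visual Analog Scale (VAS" scored 0 to 10, after the injections at visits 1 and 2. Section 9 (Data collection) lists the variable with the same object.

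Section 7.1, visit 1, describes the comparator: "The control group (CT-IM) will not receive any specific intervention other than the Polar H10 heart rate monitor". Controls are treated according to usual practice, "with the same evaluations as the intervention group (IM-IM". The end-of-session paragraph opens "At the end of the injection session (both groups), a Visual Analog Scale (VAS) will be presented to the patient to rate pain" and continues with the nurse or clinical research associate asking the patient to "rate their satisfaction with the intervention using a VAS". The visit-2 text uses the same object, but by then both arms have music.

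Section 2.3 (Hypotheses and objectives) words the construct differently: "patient satisfaction regarding the injections following the musical intervention session will be assessed". The secondary objectives in section 3.2 name patient satisfaction without saying with what.

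For analysis, section 10.4 includes satisfaction among the visit-1 outcomes that "will follow the same statistical analysis plan as for the primary endpoint", which is a t-test or Mann-Whitney test between randomized groups. It later gives satisfaction as its example of a non-repeated comparison made by those tests. It also lists satisfaction among the visit-2 outcomes to be analysed with mixed models.

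**The concern.** A between-arm difference in a rating can be read as a treatment effect only if both arms rate the same thing. Here the item asks about an intervention that one arm has had and the other has not. A music patient has an obvious object to rate. A control patient has none, and the protocol gives neither a control version of the question nor an instruction on what the word covers for that arm.

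Patient satisfaction is a listed secondary objective at both visits. If the literal wording reaches patients, a visit-1 difference mixes any effect of music on how the session was experienced with a difference in what was rated. In the waiting-list arm the object also shifts between visits, from whatever the patient took it to be at visit 1 to the music at visit 2, so the within-arm change has the same weakness. The analysis stage cannot tell afterwards what each control had in mind at visit 1.

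**Working it through.** The protocol gives no expected value, spread or target difference for satisfaction, so there is no figure of its own to reproduce. The check is a comparison of texts.

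**Step 1: who is asked.** Section 7.1 gives controls the same evaluations as the music arm, and the end-of-session paragraph covers both groups. Controls therefore receive the satisfaction item at visit 1.

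**Step 2: what is rated.** Sections 6.1.2, 7.1 (both visits) and 9 all give the object as the intervention. Without a qualifier, that word usually means the music: the abstract's brief description of the intervention presents the MUSIC CARE device, chapter 8 (Study intervention) describes the application, section 6.3 says patients without music at visit 1 are offered the intervention at visit 2, and section 7.1 calls the music arm the intervention group.

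**Step 3: what each arm has received when asked.**

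| | Visit 1 | Visit 2 |
|---|---|---|
| IM-IM | music | music |
| CT-IM | no music, chest strap only | music |

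**Step 4: which comparisons share an object, on the literal reading.**

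- Visit 1, between arms: no.
- CT-IM, visit 1 to visit 2: no.
- IM-IM, visit 1 to visit 2: yes.
- Visit 2 scores compared directly between arms: yes.
- A mixed model that takes in visit-1 satisfaction as well as visit 2: it uses the affected control ratings.

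**Step 5: reach and size.** Section 10.1 plans 40 patients per group, so at most 40 control ratings at visit 1 are involved. For scale only, suppose a fraction p of controls score 0 where they would have given the session a score s. The control mean then falls by p × s. With an assumed s = 7:

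- p = 0%: 0 × 7 = 0 points
- p = 10%: 0.10 × 7 = 0.7 points
- p = 20%: 0.20 × 7 = 1.4 points

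Both p and s are assumptions with no basis in the protocol. Controls might instead rate the care or the staff generously, which would move the mean the other way.

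**Step 6: what is untouched.** The sample size in section 10.1 rests on the LF/HF ratio (difference 1.8, standard deviation 2.3), and the primary analysis in section 10.3 does not use satisfaction.

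**The case against.** The strongest reply is that this is loose wording and not a measurement failure. Section 2.3 speaks of satisfaction regarding the injections, which both arms can rate. The objectives and the analysis section say only patient satisfaction, and the scale anchors do not mention music. Where music is meant, the protocol often writes the qualified term, and the control sentence in section 7.1 even counts the heart rate monitor as a kind of intervention. The item as shown to patients is not in the document, and a nurse or clinical research associate asks it in person and can explain it.

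Part of this stands. The injection reading is possible, so it is not certain that the arms will rate different things. But the protocol does not adopt that reading: section 2.3 conflicts with sections 6.1.2, 7.1 and 9, and its own sentence refers to satisfaction after a music session, which visit-1 controls do not have. Explanation at the bedside is no remedy either. It is not standardized, and it may come from staff who know the allocation, since the research associate performs the randomization.

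A reader might also infer that controls will score low because they were given nothing, and that the comparison therefore favours music. The document does not support this: how controls would answer is conjecture. Nor does it follow that satisfaction is lost altogether, because visit-2 scores share one object across arms.

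**Conclusion.** The point holds as an inconsistency in what the item measures. Taken literally, the visit-1 between-arm satisfaction test and the CT-IM change between visits do not rest on one common construct. This assumes that the wording in sections 6.1.2, 7.1 and 9 is what patients hear. If the item in use already asks about the injection session, the defect is confined to the protocol text.

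The reach is up to 40 control ratings. The size and direction of any distortion cannot be obtained from the document, and the 0 to 1.4 point range shows scale under stated assumptions and is not an estimate. The consequence is limited: section 10.2 makes secondary analyses exploratory, and the primary endpoint and sample size are unaffected. It should still be corrected, because a listed objective depends on it and ratings collected on an unclear item cannot be reinterpreted later.

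**What to change.** Align sections 2.3, 6.1.2, 7.1 (visits 1 and 2) and 9 on a single item that both arms can answer at both visits: satisfaction with today's injection session, 0 to 10, asked in the same words in each arm. Use that item for the visit-1 comparison and for the visit-2 analyses in section 10.4.

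If the team also wants to know how patients liked the music, a separate item can be put only to those who had it and reported descriptively. This is optional and is not needed to remove the inconsistency.

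The cost is the rewording of one scale item and its case report form field (two if the optional item is added), with no extra visit, no extra patient and no change to the injections or the music. If patients have already been rated, the report should state which wording each was given.
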